## 5.7 Concomitant Medication

No restrictions are placed on the prior or concomitant interventions (medications or therapies, rescue or subsequent treatments) allowed, other than we ask the participants to refrain from taking vitamin D supplements (including multivitamins that contain vitamin D) that exceed 400IU/day for the duration of the trial. At each treatment visit (once monthly for 6 months) and at the final assessment, researchers will ask the participant if they are taking any additional vitamin D supplements. If the participant indicates that they have been taking additional vitamin D supplements that exceeds 400 IU/day, a blood sample will be collected and tested for calcium. If the corrected calcium is above normal range, a parathyroid test will be performed. The participant will be asked to refrain from taking further vitamin D supplements that exceed 400IU/day and if they decline to do so, they will be encouraged to stay involved in the study for the full duration but no more IMP/placebo will be administered.

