**Special warnings and special precautions for use**

- During long-term treatment with a daily dose exceeding 1000 IU vitamin D the serum calcium values must be monitored.

- Special attention should be paid to patients treated with thiazide diuretics, to patients with nephrolithiasis history, to those suffering from sarcoidosis and during pregnancy. Special attention is also requested in patients with atherosclerosis, cardiac disorders, renal disorders and hyperphosphatemia. It is recommended to monitor levels of calcium, phosphates, magnesium, cholesterol (increases with higher doses) and alkaline phosphatase in serum

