**Interaction with other medicinal products and other forms of interaction**

- Digitalis (cardiac glycosides): Oral administration of vitamin D3 may increase the efficacy and toxicity of digitalis. Regular medical supervision is required including assessment of ECG, serum calcium, and possibly also digoxin plasma levels.
- Thiazide diuretics (e.g. benzothiadizine): The urinary calcium excretion may be reduced and the risk of hypercalcaemia may be increased.
- Barbiturates (e.g. phenobarbital) or phenytoin: plasma concentrations of 25-OH D may be decreased and metabolism to inactive metabolites may be increased,
- Corticosteroids: may decrease the efficiency of vitaminD3
- Vitamin D3 metabolites or analogues: It is recommended to combine with Vigantol only in exceptional cases and with monitoring of serum calcium levels.
- Rifampicin and isoniazid: may increase the metabolism of vitamin D3 and reduce its effectiveness.
- Large doses of vitamin D may cause hypercalcemia, increase cholesterolemia, lower alkaline phosphatase activity, tend to cause alkalosis
- Administration of medicaments containing magnesium aluminium (some antacids) is not recommended.

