We will also ensure that all patients are made aware of the symptoms of hypercalcaemia (loss of appetite, nausea and vomiting, constipation and abdominal pain, increased thirst and frequent urination, fatigue, weakness, and muscle pain). If any of these symptoms are detected in between dosing visits, patients will be advised to contact their GP, so that their GP can arrange for a blood test for hypercalcaemia (and report hypercalcaemia as a suspected adverse reaction to the Trial Coordinating centre). First line treatment for hypercalcaemia is simple rehydration but if this is not effective then pharmacological interventions can be used. The GP will advise of this. The research team who administer the monthly IMP/placebo dose will also ask the patient if they have experienced any of these symptoms since they were last seen by the research team, this will be done routinely every month before any IMP/placebo administration. Should these symptoms be reported at a scheduled visit, a blood test will be offered to the patient to check calcium levels and ensure patient-safety.

Participants will be asked to refrain from taking vitamin D supplements (including multivitamins containing vitamin D); however, supplementation of up to 400IU/day will be permitted throughout the trial, as recommended by Public Health England.

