| Service Contacts Form                                                                                   | X                      |               |                                                                                               |               | X                                                          |                      |                   | X                     |

\* In the event that it is not possible to obtain a urine sample, a blood HCG sample will be obtained and tested for pregnancy. No IMP will be administered without first ascertaining pregnancy status. Pregnancy tests will not be done for female participants who are permanently sterile or who are post-menopausal (no menses for 12 months without an alternative medical cause).

\*\* AEs collected from consent. Patients will be phoned 28 days post the last dose of treatment at 6 months to check for any adverse events. At dosing visits 1 – 6, we will assess adverse events in person with the participant at their scheduled visit. If no IMP is given at the Month 6 visit, no follow-up call will be needed. Should a participant withdraw from the study, AEs will need to be collected up to 28 days after their last dose.

\*\*\* Blood sampling for calcium levels (including parathyroid hormone test) will only be performed at these time points if patient reports nausea and vomiting.

\*\*\*\* The IMP is administered once a month, every month for 6 months.

\*\*\*\*\* The 9-month safety check and 12-month assessments will only be performed on those patients who have received more than 6 monthly doses of the IMP prior to the protocol change dated (02.06.17). However, the IMP/placebo will no longer be administered after 6 months.

DFEND Protocol Version 10.1 03.05.2019

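### After randomisation, no rule in the protocol is triggered when a participant without symptoms starts a cardiac glycoside or a thiazide (5.7 against 5.3 and 6.2(c)): a minor safety gap that is cheap to close

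*Combined protocol and SAP*

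**What the plan says.** **At entry.** Protocol 6.2(c) excludes anyone who took a cardiac glycoside or bendroflumethiazide in the previous month, along with several other drugs. Under 6.3 the PI or a delegated study doctor confirms eligibility before randomisation.

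**Product risks (5.3).** This section names the SmPC as the reference document and then lists warnings. On digitalis: "Regular medical supervision is required including assessment of ECG, serum calcium, and possibly also digoxin plasma levels". On thiazides: "Special attention should be paid to patients treated with thiazide diuretics" and, in the interactions list, "The urinary calcium excretion may be reduced and the risk of hypercalcaemia may be increased".

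**After randomisation (5.7).** "No restrictions are placed on the prior or concomitant interventions (medications or therapies, rescue or subsequent treatments) allowed", except vitamin D above 400 IU/day. Only that exception leads to action. If a participant reports "supplements that exceeds 400 IU/day, a blood sample will be collected and tested for calcium". Then: "If the corrected calcium is above normal range, a parathyroid test will be performed". IMP stops only if the participant declines to give up the extra vitamin D.

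**Calcium testing.** Sections 8.2 and 9.1 schedule calcium at baseline and month 3, and Table 1 in 7.1 also marks month 6. For ordinary dosing visits, the Table 1 footnote says: "Blood sampling for calcium levels (including parathyroid hormone test) will only be performed at these time points if patient reports nausea and vomiting". Section 5.3 describes a wider list of hypercalcaemia symptoms, asked about before each dose, and adds: "Should these symptoms be reported at a scheduled visit, a blood test will be offered to the patient to check calcium levels".

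**Who sees the medication list.** Table 1 marks current medication at the dosing visits and at months 3 and 6. Under 5.6 doses are given by a trained and delegated member of the research team.

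**The concern.** The protocol treats cardiac glycosides and one thiazide as reasons not to enrol, and its risk section says why these drug classes need care alongside vitamin D. Once a participant is randomised, that recognition has no working step behind it. Someone who starts digoxin or a thiazide in month 1 and feels well can be given the next 120,000 IU dose by a researcher who has just written the new drug on the worksheet and has no instruction to act on it.

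What is at stake is the safety of individual participants: raised calcium on a thiazide, or enhanced digitalis toxicity. No claim is made about the efficacy comparison.

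**Working it through.** The plan gives no figure to reproduce. The check has two parts: a comparison of the sections, and a count of the doses that can fall between calcium draws.

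**1. Is any action tied to starting the drug?**

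| Section | What it does | Triggered by a new glycoside or thiazide in someone without symptoms? |
|---|---|---|
| 6.2(c), 6.3 | Exclusion, confirmed once by a doctor | No; applies before randomisation only, and bendroflumethiazide is the only thiazide named |
| 5.7 | Calcium, then PTH if calcium is high | No; extra vitamin D only |
| 5.3 and Table 1 footnote | Calcium test for symptoms | No |
| 8.2, 9.1, Table 1 | Scheduled calcium | No; set by the calendar |
| Table 1, 7.1(a) | Current medication recorded | Recorded, with no action attached |
| 6.5 | Investigator may stop study drug | No; general discretion |
| 6.4.2, 13 | Patient card; participation entered in case notes | No; indirect |

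ECG appears only in the 5.3 interaction text and is not in the schedule. The footnote's narrower symptom list (nausea and vomiting) and the wider list in 5.3 give the same answer for someone with no symptoms.

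**2. How many doses can pass before the next scheduled draw?**

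Inputs: draws at baseline, month 3 and month 6 (Table 1), and six doses (5.6, Table 1). The count is of doses after dose 1 that fall strictly between two draws; a dose on the day of a draw is not counted.

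- *Monthly from the first dose (5.6):* doses at months 0, 1, 2, 3, 4, 5. Between baseline and month 3: months 1 and 2, so 2 doses. Between months 3 and 6: months 4 and 5, so 2 doses.
- *Sixth dose at the month 6 visit (Table 1 footnotes and 9.1), month 3 at visit 3:* visit 2 gives 1 dose; visits 4 and 5 give 2.
- *Sixth dose at the month 6 visit, month 3 at visit 4:* visits 2 and 3 give 2 doses; visit 5 gives 1.

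The range is 1 to 2 doses per interval, or 120,000 to 2 × 120,000 = 240,000 IU. The count of 1 comes only from readings that fit five gaps between doses into six months, which sits poorly with the monthly spacing in 5.6. Under 5.6 itself the count is 2. It could be higher if a draw is late, because 5.6 sets no upper time limit for safety bloods. If 8.2 and 9.1 were followed without Table 1, there would be no scheduled draw after month 3.

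**The case against.** The case for leaving the text alone is substantial.

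- **Cover already exists.** Hypercalcaemia symptoms are asked about before every dose, calcium is checked in everyone at month 3 (and at month 6 per Table 1), and medication is recorded monthly. Entry excludes corrected calcium above 2.6 mmol/L, past hypercalcaemia, renal dysfunction, renal stones, sarcoidosis and parathyroid disease. The dose was chosen as one regarded as safe in pregnancy, and 6.5 lets the investigator stop study drug. All of this stands and keeps the point minor. It does not answer it, because none of these steps is set off by the new drug and symptom questions cannot find asymptomatic hypercalcaemia.
- **5.7 does not cancel 5.3.** Not prohibiting a drug is different from ignoring it, and study SOPs exist outside these documents. This also stands: the precautions in 5.3 remain in force. What is missing is the step that carries them out.
- **5.3 assigns no trial procedure.** A reader might infer that the trial team must perform ECGs. The documents do not say so: 5.3 does not state who supervises, and the prescriber of a glycoside could do it. For thiazides 5.3 specifies no test or interval. The fix should therefore ask the study doctor to confirm supervision of a glycoside, without adding ECGs to the trial.
- **Calcium above normal range is not a stopping rule.** A reader might infer from 5.7 and 9.1 that it already stops IMP. In both places it leads only to a PTH test. An automatic stop would be a new rule, and stricter than the one for a participant taking extra vitamin D with the same result.

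**Conclusion.** The gap is real and minor. The protocol names these drugs as a risk at entry and in 5.3, and no section found ties any action to a participant without symptoms starting one after randomisation. Following 5.7 as written lets one or two further doses be given before the next scheduled calcium draw.

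The documents do not say how many participants would start either drug. It is probably few, although eligibility runs to age 65. With 1:1 allocation about half would be on placebo, but staff are blinded, so a rule has to cover both arms. The conclusion assumes that no operational document outside the protocol and SAP already supplies the step.

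A reader might go further and conclude that such participants are unmonitored. The documents do not support that, given the scheduled calcium and monthly symptom questions.

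**What to change.** Add to 5.7:

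- At each dosing visit, check the recorded medication list for a newly started cardiac glycoside or any thiazide diuretic (the class, as in 5.3).
- If one is found, hold that visit's dose and take a corrected calcium, with PTH if it is above normal range, as 5.7 already does for extra vitamin D.
- Refer to the PI or delegated study doctor, who decides whether IMP continues. For a glycoside, the doctor also confirms that the treating team knows of trial participation and is providing the supervision described in 5.3.
- Leave the response to a raised calcium to that doctor, with no automatic stop.
- Participants taken off IMP stay in follow-up, in line with 5.6 and 6.5.

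**Cost.** One worksheet line, an occasional calcium test, a brief doctor review (with contact with the treating team for a glycoside), and a few delayed or missed doses. The existing dosing rules absorb a delay. A month of dosing is 120,000 / 4,000 = 30 days. A held dose given at the end of the +2 week window leaves 30 − 14 = 16 days to the next scheduled visit. The 24-day minimum then moves that visit by 24 − 16 = 8 days, still inside its own +2 week window. A dose that cannot be given in time is logged as a deviation under 5.6.

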## 6. Selection and Withdrawal of Subjects

### 6.1 Inclusion Criteria

All patients within EIS and FEP inpatient units who meet the following criteria will be invited to participate in the study:

- a) Aged between 18-65 years old including women of child-bearing age
- b) Having a diagnosis of functional psychosis FEP defined according to ICD-10 criteria for psychosis (codes F20-29 and F30-33)
- c) Willing to agree to refrain from taking multivitamin or non-study vitamin D supplements that exceed 400IU/day throughout the study
- d) Willing to give a blood vitamin D sample at baseline
- e) Patients who are able and have given written informed consent

### 6.2 Exclusion Criteria

- a) Known intolerance of Vitamin D2 or D3 or known allergy to any of the trial medications
- b) Those who are currently taking vitamin D supplements at a dose exceeding 400IU/day
- c) Those who have taken cardiac glycosides; calcium channel blockers; or oral, intramuscular, or intravenous corticosteroids; bendroflumethiazide; isoniazid; or rifampicin in the past one-month
- d) Known active tuberculosis, sarcoidosis, hypo or hyperparathyroidism, past or present nephrolithiasis (renal stones), suspected or diagnosed hepatic or renal dysfunction, any malignancy other than non-melanoma skin cancer not in remission for  $\geq 3$  years, calcium disorders
- e) Baseline corrected serum calcium  $> 2.6\text{mmol/L}$
- f) Patients with known history of hypercalcaemia
- g) Pregnant or breast-feeding women and women planning a pregnancy
- h) Patients lacking the capacity to provide written informed consent
- i) Those who do not have sufficient English to complete the core assessments with the available assistance

### 6.3 Selection of Participants and informed consent

The study population is patients in their first episode of psychosis (FEP) defined as first presentation to services within the last three years. Participants will be recruited from NHS Trust research sites (including Early Intervention Services, Home Treatment Teams, Inpatient Units, Community Teams and Participant Identification Centres (PIC)). Where participants are recruited from PICs consent and other trial activities will be undertaken at the host research site. To be eligible for entry into the trial individuals must satisfy all of the inclusion criteria and none of the exclusion criteria. The eligibility criteria are purposefully minimal to facilitate the enrolment process and to maximise generalisability of the trial results, namely individuals diagnosed with first episode psychosis attending clinical services.

An ICH-GCP trained clinician (research nurse, doctor or allied health professional) will be responsible for obtaining written informed consent from all trial participants prior to baseline assessment. Eligibility will be confirmed before randomisation by the PI or delegated study doctor **only**.

Subjects will be offered £80, in total, as reimbursement for the time they give to participating in the trial. £20 will be offered at baseline, £20 at the 3 month safety check, and a final £40 after the final assessment. Reasonable travel expenses incurred whilst traveling both to and from study appointments will also be reimbursed. Participants active in the study at the time of this change will receive a total of £80. The new payment schedule will be adhered to for baseline and Month 3, and any extra amount will be paid at the Month 6 assessment.

### 6.4 Randomisation Procedure / Code Break

#### 6.4.1 Randomisation

An online randomisation service will be provided by King's Clinical Trials Unit. Randomisation will take place after collection of baseline measures. The unit of randomisation will be the individual participant. Randomisation will be at a 1:1 ratio and the method of randomisation will be stratified randomisation with randomly varying block sizes of 2-4 where the stratification factor is ethnicity (with 2 levels: White, Other).

We chose to balance treatment arms by ethnicity as this is thought to predict outcomes. There are no known predictors of PANSS in our target population. However, blood vitamin D concentration varies by ethnicity; and we hypothesize that blood vitamin D concentration mediates any effect of vitamin supplement. Thus ethnicity was chosen as a randomisation stratifier.

Each active and placebo IMP bottle will have a unique identification number. Each patient will be assigned a unique Patient Identification Number (PIN) which will be used throughout the duration of their treatment. To request randomisation service user accounts and/or email notifications of randomized patients contact the DFEND trial manger on [[contact]](mailto:[contact]).

The procedure is as follows:

1. Informed Consent is obtained
2. Baseline blood samples are taken as part of baseline assessment to confirm eligibility
3. Once the participant is found to be eligible, a trained/delegated researcher will input registration/eligibility information into the EDC Macro v4.0 to obtain a PIN.
4. This PIN and other key identifying information (Name/DOB/ethnicity) is then inputted by the trained researcher into the randomisation online system.
5. Once the information is submitted, the online system, which is managed by the King's Clinical Trials Unit (KCTU), then will randomly allocate the patient to a study arm and notify the unblinded members of staff, which are currently: the CRA from the KHP CTO (sponsor office), the trial pharmacy staff and the emergency code breaking service. The blinded members of staff should include all research teams at site level including the study site PI.

If any errors are made in the request (e.g. incorrect patient initials, date of birth or stratification factors), as soon as the error is noticed by the researcher inputting the information, they should contact the trial manager and the randomisation service team on [[contact]](mailto:[contact]) and it will be logged on the system. A randomisation cannot be 'undone' where incorrect stratification factors have been used, so care will be taken when requesting randomisation. However information about errors can be recorded alongside the randomisation data for that patient, so that this key information is not missed.

#### **6.4.2 Emergency Code Break**

24hr Emergency Code Break and Medical Information will be provided by ESMS Global Ltd. Each randomised subject will be provided with a patient card detailing code break telephone numbers and emergency contact details. Subjects will be requested to carry this card with them at all times whilst participating in the trial. The only people authorised to make emergency enquiries to the code breaking service are healthcare professionals who have direct responsibility for the care of the trial subject concerned (clinical trial investigators, pharmacists and the KHP CTO staff are also authorised to request unblinding). The subjects themselves, their relatives or other members of the public are not authorised users and if they use the number and request unblinding they will be directed to contact their trial team and/or local PI.

#### **6.5 Withdrawal of Subjects**

Participants have the right to withdraw from the study at any time for any (or no) reason. The investigator also has the right to discontinue patients from the study drug in the event of AEs, SAE's, SUSAR's, protocol violations, administrative or other reasons. It is understood by all concerned that an excessive rate of withdrawals can render the study un-interpretable; therefore, unnecessary withdrawal of patients should be avoided. Should a patient decide to withdraw from the study, all efforts will be made to report the reason for withdrawal as thoroughly as possible. Should a patient wish to discontinue the study drug only, efforts will be made to continue to collect follow-up data, with the permission of the patient.

In light of substantial changes to the study duration, all participants will be informed of changes made to the study initially by letter and again in person at the next patient visit. They will be

provided with a new patient information sheet, and will be invited to sign and date a new consent form. Those participants who do not agree to the new protocol changes will be withdrawn from the study.

Specifically, for those participants who originally consented to a 12 month trial and who have received more than 6 monthly doses of the IMP, we will still perform the 9 month safety blood test and conduct the 12 month follow up assessments as originally planned (see Table 1). The only change will be that these participants will receive no further doses of IMP.

For those participants who originally signed up to a 12 month trial and who have received less than 6 monthly doses of the IMP until 02.06.17, we will invite patients to give consent to the new consent form (V8a 02.06.17) which states that the trial will end at the 6 month follow-up assessment mark, after which no further IMP will be dosed. We will honour the original total planned payment described in ICF v7 02.12.2016 and PIS v8 02.12.2016: £5 at the 9 month safety check and £10 at the 12 month follow-up assessment. This total of £15 will be paid at the 6 month visit.

